#### Health risk behaviours

The STEPS tobacco modules will be used to assess tobacco-related behaviours.^29^

#### Alcohol consumption

The STEPS alcohol module will be used to determine lifetime abstainers, past 12 months abstainers and current users of alcohol using the WHO cut-off scores.^29^

#### Diet

The STEPS diet module will be used to record the number of days that respondents consumed fruit and vegetables in a typical week, and the number of servings of fruit and vegetables consumed on average per day.^36^

#### Physical activity

The STEPS physical activity module will be used to record activity for transport purposes (eg, walking, cycling), vigorous and moderate activity at work and vigorous and moderate activity in leisure time and time spent sitting. Show cards with culturally relevant examples will be used to aid respondents in classifying activities. Analysis and categorisation will follow the WHO guidelines.^37^

#### Non-communicable diseases

Any medically diagnosed history of raised blood pressure (BP), heart disease, hypercholesterolemia and high blood glucose, and treatment advised by a health worker for these diseases (such as prescribed medicines, a special diet, advice to reduce salt intake, lose weight, stop smoking or do more exercise) will be collected using the STEPS module for non-communicable diseases. Lung disease is not included in the STEPSs survey. However, it will be recorded asking the same set of questions as the non-communicable diseases included in the STEPS survey.

#### Infectious diseases

Self-report of medically diagnosed history of hepatitis B, C, syphilis, tuberculosis, HIV and intestinal parasites will be recorded.

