In South Asia, rates of mental illness and physical non-communicable diseases have been increasing rapidly.^13 14^ This increase, coupled with the lack of access to even basic mental healthcare,^15^ and neglect of the physical health needs of people with SMI by policymakers and healthcare services,^16^ means that the burden of disease due to physical disorders in people with mental illness. is set to rise further, with a corresponding increase within country and global health inequalities. This increase is coupled with a recognised lack of information about the prevalence of physical conditions and health risk behaviours in the SMI population in South Asia.^17^ This gap in knowledge, particularly in relation to health service planning in LMICs, has been pointed out repeatedly as a priority for research.^18^ Addressing mental and physical health comorbidity in LMICs is also a global priority, recognised in global policies to help achieve the sustainable development goals, including ‘ensuring healthy lives and promoting well-being for all’.^19–21^ A detailed understanding of the prevalence of physical health conditions, health risk behaviours and health service utilisation in SMI in LMICs is needed to progress this agenda.^22^

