### Objectives

In people with SMI attending specialist mental health facilities:

Determine the prevalence of physical health conditions (ie, type 2 diabetes, hypertension, heart disease, obesity and infectious diseases) and health-risk behaviours (ie, diet, physical activity, alcohol and tobacco use) and compare these findings with those reported in the general population.Determine the association between physical health conditions, health-risk behaviours, health-related quality of life and various demographic, behavioural, cognitive, psychological and social variables.Identify health-service utilisation and the type of lifestyle advice that has been offered for this population.Support clinical trial readiness by providing evidence-based findings regarding outcome measures and procedures relevant for clinical trial design.

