### Sample size

We aim to build as large a sample as possible within the resources available over the study period (n=1500 per country). As an indicative example of survey precision to address some of the key research questions, we provide a sample size estimate for investigating the prevalence of diabetes. Assuming a prevalence estimate of 10% (based on results from previous studies,^24^ we will need 857 participants per country to achieve ±2% precision assuming a 95% CI.^25^

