### Data collection

We will conduct a face-to-face digital survey to collect information about physical health and health-risk behaviours, severity of common mental disorders and health-related quality of life using validated instruments as described below. The survey has been translated into the most common languages in the countries (Urdu in Pakistan, Bangla in Bangladesh and Hindi, Kannada, Tamil and Telugu in India). The team of interviewers in each county will include men and women and will include researchers who speak regional dialects, which is consistent with usual clinical practice in these settings.^28^ Participants will be able to express a preference to be interviewed by a researcher of the same gender, to reduce response bias that might arise due to the gender of the interviewer.

The WHO STEPwise approach to Surveillance (STEPS) instrument V. 3.2 will be used to collect information about non-communicable diseases and related health-risk behaviours.^29^ STEPS is an international standardised tool that will allow comparisons with the general population within the country and between countries.^30^ The instrument has already been translated, used and validated in the general population in Bangladesh, India and Pakistan.^31–33^

To allow patients to disclose information on sexually transmitted diseases, HIV diagnosis, alcohol and tobacco consumption, in agreement with patient’s wishes, the interviewer will ask the caregivers/attendants to leave the room for this part of the interview.

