#### Biochemical analysis

A blood sample (8–9 mL) will be taken from consenting participants for glycated haemoglobin (HbA1c), lipid profile (triglycerides, total cholesterol, high-density lipoproteins (HDL), low-density lipoproteins (LDL)), thyroid function tests (includes thyroid hormones (T3, T4), thyroid stimulating hormone (TSH)), liver function tests (total bilirubin, aspartate transaminase (AST), alanine aminotransferase (ALT), alkaline phosphatase (ALP), total protein, albumin, albumin to globulin ratio), creatinine and haemoglobin.

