### Statistical analysis

Quantitative data will be summarised using descriptive statistics. First, prevalence rates of infectious diseases, long-term physical health conditions (eg, diabetes, heart disease) and health-risk behaviours for type II diabetes, cardiovascular and respiratory disorders (eg, tobacco use, obesity, physical activity, diet) will be estimated in the SMI population. Second, we will examine the associations between physical health conditions and health-risk behaviours, using regression models with random intercepts for data collection site with the following potential covariates: demographic variables (ie, age, sex and level of education), history of mental and physical conditions and biomarkers (eg, body mass index, BP). These regression models will also be used to calculate prevalence rates of physical health conditions and health-risk behaviours adjusted for these covariates (eg, for comparison with external general population data). Further regression analyses will explore the association between mental and physical health conditions and health-related quality of life measured using EQ-5D-5L. Regression models will take account of the nature and distribution of data (eg, count vs continuous data; skewed vs normally distributed data). To investigate the prevalence of physical health conditions and health risk behaviours in the general population, we will extract aggregated data on the prevalence of physical health conditions, health risk behaviours and lifestyle advice from the last available WHO STEPS survey from Bangladesh,^44^ India^45^ and Pakistan.^46^

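### Objective 1 promises the prevalence of infectious diseases, but the stated measure gives only the proportion who report ever having had a medical diagnosis

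*Protocol article*

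**What the plan says.** In the protocol article, the first objective reads: "Determine the prevalence of physical health conditions (ie, type 2 diabetes, hypertension, heart disease, obesity and infectious diseases". Infectious diseases thus stand in the list of conditions to be estimated, with no qualifier. The Statistical analysis section does the same and plans to estimate "prevalence rates of infectious diseases, long-term physical health conditions (eg, diabetes, heart disease" in people with SMI.

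The section on infectious diseases is a single sentence: "Self-report of medically diagnosed history of hepatitis B, C, syphilis, tuberculosis, HIV and intestinal parasites will be recorded". It covers six infections. It states no time window and no question on current status or treatment.

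The Biochemical analysis section begins "A blood sample (8–9 mL) will be taken from consenting participants for glycated haemoglobin (HbA1c), lipid profile" and goes on to thyroid function, liver function, creatinine and haemoglobin. No serology or other infection test is listed.

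The limitations, both in the box after the abstract and in the Discussion, deal with the specialist-centre sample. The Discussion adds the lack of a control group. Neither mentions how infection is ascertained.

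**The concern.** The quantity promised and the quantity measured differ. A reported history of diagnosis counts a person only if the infection was at some time tested for or recognised, the person was told, and the person discloses it. Infections that can be silent for long periods (hepatitis B and C, HIV, latent syphilis) are missed wherever nobody tested. For infections that resolve or are cured (tuberculosis, syphilis, intestinal parasites), the same question includes illness that is over. Under-diagnosis is plausible on the article's own account, since the Background describes "neglect of the physical health needs of people with SMI by policymakers and healthcare services". That remark is about physical health in general, not infection testing, so it supports the direction of the error but not its size.

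At stake is what the study may conclude. A low figure for HIV or hepatitis, published as prevalence, could be read as low need when it partly reflects low testing. A figure for tuberculosis or parasites could be read as current burden. Associations with behaviours would partly reflect who was tested. If the history variable enters the EQ-5D-5L models, present health would be related in part to past episodes. No later analysis can recover undiagnosed infection from these data.

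**Working it through.** **1. The plan's own figure.** The only precision calculation is for diabetes (Sample size section: 10% prevalence, ±2%, 95% CI, 857 per country). The single-proportion formula gives n = 1.96² × 0.10 × 0.90 / 0.02² ≈ 864, within 1% of 857. A finite-population correction with an assumed population of 100,000 gives 864.3 / (1 + 863.3/100,000) = 856.9. This figure is sound, but it says nothing about infections. The article gives no expected infection prevalence and no diagnosed share.

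**2. Promise against measure.** Objectives and Statistical analysis: prevalence of infectious diseases. Infectious diseases section: self-reported diagnosed history. Biochemical analysis: no infection test. For diabetes and hypertension the reported history is backed by HbA1c and measured blood pressure. For infections nothing backs it.

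**3. What the measure estimates.** Let C be the proportion currently infected, R the proportion with a past infection now resolved, and s the share of these who were diagnosed and disclose it. For simplicity s is taken as the same for both groups, and nobody reports a diagnosis they did not have. Then

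expected survey figure = s × (C + R).

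This equals lifetime prevalence (C + R) only if s = 1. It equals current prevalence C only if s = 1 and R = 0, or if the two errors happen to cancel.

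**4. Missed diagnosis alone.** Assume C = 4% and R = 0. The half-width is 1.96 × √(p(1−p)/1500) at the planned 1500 per country.

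| s (assumed) | Reported p | Bias (points) | 95% half-width (points) |
|---|---|---|---|
| 0.10 | 0.04 × 0.10 = 0.4% | −3.6 | 0.3 |
| 0.50 | 0.04 × 0.50 = 2.0% | −2.0 | 0.7 |
| 0.80 | 0.04 × 0.80 = 3.2% | −0.8 | 0.9 |

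**5. Both errors together.** Assume C = 3% and R = 3%, so lifetime prevalence is 6%.

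| s (assumed) | Reported p | Bias against current (points) | Bias against lifetime (points) |
|---|---|---|---|
| 0.2 | 0.2 × 6% = 1.2% | −1.8 | −4.8 |
| 0.5 | 0.5 × 6% = 3.0% | 0 | −3.0 |
| 0.8 | 0.8 × 6% = 4.8% | +1.8 | −1.2 |
| 1.0 | 1.0 × 6% = 6.0% | +3.0 | 0 |

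The half-widths at n = 1500 run from about 0.5 to 1.2 points. The sign of the error against current prevalence depends on s, which the survey does not observe.

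**6. Sample size.** n does not appear in s × (C + R). In the last row of step 4, going from 1500 to the pooled 4500 (ignoring clustering by site) shrinks the half-width from 0.89 to 0.89/√3 ≈ 0.51 points. The bias stays at −0.8.

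**The case against.** Several points on the other side stand.

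- The measure is disclosed. The section on infections says plainly that it is self-report of diagnosis, and nothing claims serology. A careful reader can work out what the prevalence figure will mean. The fault lies in the unqualified label in the Objectives and Statistical analysis and in the silent limitations, not in any concealment.
- Diagnosed history is a legitimate measure, and infections are not alone in resting on it. Heart disease and lung disease are recorded by history too. A reader might infer that infections are the single exception among objectively measured conditions, and that is not so. This does not cure the label for infections.
- A reader might infer that the questionnaire has no item on current status or treatment. The article condenses the instrument into one sentence, so the absence of such an item cannot be established. Which variable enters the EQ-5D-5L models is likewise a matter for the analysis plan.
- A reader might infer that the confidence interval would exclude the true value. That depends on the assumed ascertainment. With 4% true and 80% diagnosed and disclosed, the interval is 3.2% ± 0.9, about 2.3% to 4.1%, and it contains 4%.
- Counting resolved episodes is an error only for infections that resolve or are cured. For lasting infections the issue is missed diagnosis.
- The plan asks caregivers to leave the room, if the patient wishes, for questions on sexually transmitted diseases and HIV. This helps disclosure. It cannot reveal an infection that was never tested for.
- The abstract speaks only of physical health conditions and does not name infections, so its wording is not at fault.

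**Conclusion.** The point holds as a mismatch between what is promised and what is measured. Followed as written, the plan would report as prevalence a figure that misses undiagnosed infection and, for infections that can be cured, includes past episodes. That conclusion needs only that some infections are undiagnosed or undisclosed, or that some reported ones have resolved.

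The size is unknown from the documents. On an assumed true prevalence of 4% with 10% to 80% diagnosed and disclosed, the shortfall is 0.8 to 3.6 points. With resolved infections included, the error against current prevalence can go either way. These are illustrations, and none of the input rates comes from the article.

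The documents do not support saying that the item is invalid in itself, that the interval must miss the truth, or that the questionnaire lacks a current-status question. Because the estimand is misnamed in an objective and the correction is nearly free, it should be made.

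**What to change.** In the Objectives and in the Statistical analysis section, restate this outcome as a self-reported, medically diagnosed history of infectious disease, and say that it does not estimate current or undiagnosed infection. Add the same point to the limitations in the box after the abstract and in the Discussion. Interpret associations with health-risk behaviours and EQ-5D-5L as associations with reported diagnosis, which depends on access to testing.

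If the full questionnaire already records current status or treatment for infections, use that item for tuberculosis, syphilis and parasites in the EQ-5D-5L models. If it does not, a short follow-on item for those answering yes is optional. It would need translation into the survey languages and notification of the ethics committees. It would separate past from current illness among diagnosed participants, but it would still not detect undiagnosed infection, so the relabelling is needed either way. Serology is not required for this correction.

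The cost of the essential change is a few sentences and a narrower claim for this part of Objective 1.

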#### Risk behaviours related to sexually transmitted diseases

Risk behaviours related to sexually transmitted diseases will be assessed using three questions that examine the presence of multiple sexual partners, unprotected sexual contact and use of injectable drugs that have been adapted from the 10-item HIV risk Screening Instrument.^38^ This instrument has been previously used in research involving persons with SMI in India.^39^

#### Health-related quality of life

The EQ-5D-5L will be used to measure health-related quality of life.^40 41^ The EQ-5D-5L is a standardised measure of health status, it provides a simple, generic measure of health for clinical and economic appraisal. The impact of disease/disorder is characterised on five dimensions (mobility, self-care, ability to undertake usual activities, pain and anxiety/depression). The EQ-5D-5L further assesses a patient’s subjective evaluation of their health state based on a visual analogue scale (EQ-5D-VAS) between ‘0—worst imaginable health state’ and ‘100—best imaginable health state’. We will use validated translations provided by EurOQol.

#### BP and heart rate

BP and pulse rate will be taken three times using an automated BP measuring instrument (OMRON). For BP measurement, the participant must be comfortable and rested. If he/she had been exerting themselves, then there will be a minimum of a 15 min rest period before the recording is taken. There should be at least a 3 min gap between the BP recordings. The procedure will follow the stepwise instructions in the WHO STEPS surveillance manual.^42^

#### Height weight and waist circumference

Height will be measured to a precision of 0.1 cm using a portable height measuring board without footwear and headgear. Weight will be measured in kilograms using a portable weighing scale placed on a firm flat surface with light clothing and without footwear and socks. Waist circumference will be measured in a precision of 0.1 cm, using a flexible fibreglass anthropometric tape at the end of normal expiration, at the midpoint between the lower margin of the last palpable rib and the top of the iliac crest (hip bone), with the arms relaxed at the sides. All measurements will be taken in duplicate and the average of the two values will be recorded and the protocols of the WHO STEPS surveillance manual will be followed.^42^

#### Biochemical analysis

A blood sample (8–9 mL) will be taken from consenting participants for glycated haemoglobin (HbA1c), lipid profile (triglycerides, total cholesterol, high-density lipoproteins (HDL), low-density lipoproteins (LDL)), thyroid function tests (includes thyroid hormones (T3, T4), thyroid stimulating hormone (TSH)), liver function tests (total bilirubin, aspartate transaminase (AST), alanine aminotransferase (ALT), alkaline phosphatase (ALP), total protein, albumin, albumin to globulin ratio), creatinine and haemoglobin.

### Data management

To ensure quality of collected data, validation, checking, proofing and cleaning procedures will be carried out according to standard procedures.^43^ All consent forms will be stored separately from survey data in locked cabinets in locked offices at study research offices at each study site. All coded data will be transferred to and stored as anonymous data at the University of York, which will act as the data curator. A secure password protected and encrypted electronic database will be set up to store the data.

### Statistical analysis

Quantitative data will be summarised using descriptive statistics. First, prevalence rates of infectious diseases, long-term physical health conditions (eg, diabetes, heart disease) and health-risk behaviours for type II diabetes, cardiovascular and respiratory disorders (eg, tobacco use, obesity, physical activity, diet) will be estimated in the SMI population. Second, we will examine the associations between physical health conditions and health-risk behaviours, using regression models with random intercepts for data collection site with the following potential covariates: demographic variables (ie, age, sex and level of education), history of mental and physical conditions and biomarkers (eg, body mass index, BP). These regression models will also be used to calculate prevalence rates of physical health conditions and health-risk behaviours adjusted for these covariates (eg, for comparison with external general population data). Further regression analyses will explore the association between mental and physical health conditions and health-related quality of life measured using EQ-5D-5L. Regression models will take account of the nature and distribution of data (eg, count vs continuous data; skewed vs normally distributed data). To investigate the prevalence of physical health conditions and health risk behaviours in the general population, we will extract aggregated data on the prevalence of physical health conditions, health risk behaviours and lifestyle advice from the last available WHO STEPS survey from Bangladesh,^44^ India^45^ and Pakistan.^46^

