## Methods and analysis

### Design, settings and population

We will conduct a cross-sectional survey among patients with a clinical diagnosis of SMI recruited at national specialist mental health institutions. In Bangladesh, the study will be conducted at the National Institute of Mental Health and Hospital (NIMHH) in Dhaka. NIMHH offers 200 beds for in-patient care and on average 400 outpatients attend every day. In India, the study will be conducted at the National Institute of Mental Health and Neurosciences (NIMHANS) in Bengaluru, with 650 beds for in-patient care; on average at NIMHANS, 400 outpatients attend every day. In Pakistan, the study will be conducted at the Institute of Psychiatry (IOP) Rawalpindi Medical University, a WHO collaborating centre for the Eastern Mediterranean. IOP offers 60 beds for inpatients and on average 400 outpatients attend every day. All three national institutes serve patients from all over the country. Adults (18 years and over) with a clinical diagnosis of SMI (defined by the International Classification of Disease 10th revision (ICD-10^23^) as schizophrenia, schizotypal and delusional disorders (F20-F29); bipolar affective disorder (F30, F31) and severe depression with psychotic symptoms (F32.3, F33.3)),^23^ who are able to provide informed consent as assessed by the treating clinician will be recruited. Patients who lack capacity to provide consent or are unable to complete study questionnaires will be excluded (figure 1). The data will be collected from June 2019 to September 2020.

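### Relating behaviours to conditions in one cross-section without separating previously diagnosed from newly detected cases can attenuate the Objective 2 associations

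*Protocol article*

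**What the plan says.** The design is a single survey (Design, settings and population): "We will conduct a cross-sectional survey among patients with a clinical diagnosis of SMI". Objective 2 is to "Determine the association between physical health conditions, health-risk behaviours, health-related quality of life" and other variables.

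Information on conditions comes from two sources. The Non-communicable diseases section records "Any medically diagnosed history of raised blood pressure (BP), heart disease, hypercholesterolemia and high blood glucose", together with treatment advised for these diseases, including "advice to reduce salt intake, lose weight, stop smoking or do more exercise) will be collected using the STEPS module". Separately, blood pressure is measured, and under Biochemical analysis "A blood sample (8–9 mL) will be taken from consenting participants for glycated haemoglobin (HbA1c" and a lipid profile, among other tests. The Ethics section provides for abnormalities found by the research assessments to be passed to the treating clinician, so previously unknown cases are expected.

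The Statistical analysis section says that "we will examine the associations between physical health conditions and health-risk behaviours, using regression models with random intercepts for data collection site". The potential covariates include "history of mental and physical conditions and biomarkers (eg, body mass index, BP" and other measures. The same section speaks of "health-risk behaviours for type II diabetes, cardiovascular and respiratory disorders". It does not say that cases will be separated by whether they were already diagnosed. The limitations, in the summary box and the Discussion, cover representativeness and the lack of a control group; they do not mention temporality.

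**The concern.** A behaviour recorded on the survey day may have been changed by a diagnosis made before it. The protocol itself names the route: advice on salt, weight, smoking and exercise given for raised blood pressure, heart disease, cholesterol and glucose. A person first found to have raised HbA1c or blood pressure by the survey has not had that diagnosis and so has not been advised because of it. One pooled case group mixes behaviour that may have changed after diagnosis with behaviour that has not.

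At stake is the reading of Objective 2. A behaviour that is associated with a condition before diagnosis could appear weakly related to it or, under less common circumstances, unrelated or inversely related. Because the analysis section presents these as risk behaviours for the diseases concerned, readers are likely to take a weak estimate as evidence that the behaviour matters little in this population.

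**Working it through.** **The plan's own figure.** The Sample size section gives 857 per country for ±2% around 10% diabetes prevalence. The standard formula gives 1.96² × 0.10 × 0.90 / 0.02² = 864.3, so 865, which is within 1% of 857. The point here does not depend on it; only the 10% prevalence and the planned n = 4500 are used below.

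**Inputs not in the documents (assumed).** Behaviour prevalence in non-cases b0 = 30%; true odds ratio before diagnosis 1.50; share of cases already diagnosed k = 30% to 70%; share q of diagnosed users who have since stopped = 0% to 50%. Non-cases and newly detected cases are taken not to have changed.

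**Step 1, prevalence in cases before diagnosis.** Odds in non-cases = 0.30/0.70 = 0.4286. Odds in cases = 1.5 × 0.4286 = 0.6429, so b1 = 0.6429/1.6429 = 0.391.

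**Step 2, pooled odds ratio.** Observed prevalence in cases = b1 × (1 − k × q). Its odds are divided by 0.4286.

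| k | q | Observed prevalence in cases | Pooled odds ratio |
|---|---|---|---|
| 0.5 | 0.2 | 0.352 | 1.27 |
| 0.5 | 0.3 | 0.333 | 1.16 |
| 0.5 | 0.5 | 0.293 | 0.97 |
| 0.7 | 0.5 | 0.254 | 0.80 |

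**Step 3, what the pooling hides.** With q = 0.2, 0.3 and 0.5, diagnosed cases alone would show odds ratios of 1.06, 0.88 and 0.57, while newly detected cases stay at 1.50.

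**Step 4, how much change brings the pooled odds ratio to 1.0.** This needs q = (1 − b0/b1)/k = (1 − 0.30/0.391)/k = 0.233/k, that is 78%, 47% and 33% for k = 0.3, 0.5 and 0.7. At b0 = 50% (b1 = 0.60) it is 0.167/k, that is 56%, 33% and 24%. For a true odds ratio of 2.0 and b0 = 30% it is 70% and 50% at k = 0.5 and 0.7, and cannot be reached at k = 0.3. Some attenuation therefore occurs whenever any diagnosed users have stopped; reversal is much more demanding.

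**Step 5, can the groups be separated?** At 10% prevalence, 4500 participants give about 450 diabetes cases and 4050 non-cases. With an assumed equal split there are 225 per group. At 30% behaviour prevalence the variance of the log odds ratio is 1/67.5 + 1/157.5 + 1/1215 + 1/2835 = 0.0223, so the standard error is 0.149 and the 95% interval is the estimate divided and multiplied by exp(1.96 × 0.149) = 1.34. For all 450 cases pooled, 1/135 + 1/315 + 1/1215 + 1/2835 = 0.0118, giving a factor of 1.24. Per country (75 cases per group, 1350 non-cases) the factor is 1.66. The split is workable across countries and weak within one.

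**Step 6, the covariate.** If a condition is defined as diagnosed history or a raised measurement, everyone with that history is a case. Adjusting for it conditions on part of the outcome and does not report the two groups.

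**The case against.** Several objections carry weight.

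- **This may belong to the full analysis plan.** That plan is not shown and may define known and new cases. The article does, however, state the model and name the covariates, and there diagnosis history appears only as a possible adjustment.
- **Diagnosis history is already in the model.** If behaviour were the outcome and condition-specific history were entered beside current disease status, the model would come close to separating the groups. The article fixes neither that direction nor that coding, and with the condition as outcome it fails as in Step 6.
- **Advice may be rare.** A reader might infer that diagnosed patients are told to change. The protocol only records whether advice was given, finding out is Objective 3, and the Background describes neglect of physical health in this group. The bias could be small.
- **Behaviours are not all recorded as current only.** The alcohol section separates lifetime abstainers, past-12-month abstainers and current users, and the tobacco section does not limit itself to current use. This stands, and makes the remedy easier.
- **Only association is claimed.** True of Objective 2, although calling these risk behaviours for the diseases invites a causal reading.
- **The newly detected group is selected.** Being undiagnosed may depend on contact with care, severity and education. Its blood pressure cases rest on one survey assessment, and someone unaffected by one condition may have been advised for another. This is a sound reason not to make that contrast the main analysis.

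**Conclusion.** The point holds as a risk of attenuation of unknown size. It rests on two things the documents support, namely that both kinds of case will be present and that advice for the diagnosed conditions concerns the same behaviours, and on one they do not settle, namely how many diagnosed patients changed. On the assumed inputs with half of cases diagnosed, a true odds ratio of 1.50 is observed as 1.27 to 0.97 when 20% to 50% of diagnosed users have stopped.

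Three stronger readings are not supported. That associations will be reversed: at a 30% baseline and odds ratio 1.50, between 33% and 78% of diagnosed users would have to stop before the pooled value even reaches 1.0. That the plan regresses conditions on behaviours: the text speaks of associations between them and fixes no direction. That later intervention trials would be misdirected: Objective 4 concerns outcome measures and procedures for trial design, not which behaviours cause disease.

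**What to change.** In the Statistical analysis section:

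1. For diabetes, hypertension and raised cholesterol, code each participant as previously diagnosed, newly detected by the survey (raised HbA1c, blood pressure or cholesterol without diagnosed history), or unaffected.
2. Prespecify behaviour associations for each case group against unaffected, reported beside the pooled model and not in place of it.
3. Use former-use or ever-use categories for tobacco and alcohol where they are collected.
4. Describe associations for conditions known only by self-report (heart and lung disease) as non-directional, and add temporality to the limitations.

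The cost is recoding of data already collected and an additional analysis per condition. The price is precision: about 225 diabetes cases per group overall under an equal split, with an interval factor of about 1.34 against 1.24 pooled, and about 75 per group and 1.66 within a country, before any refusals of blood sampling. The newly detected contrast is less prone to this bias but not free of it, and should be described in that way.
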